## D.9. Data management and statistical analysis

Descriptive data analysis will be performed and selected demographic and environmental characteristics such age, sex, tribe/religion, household size, socio-economic/educational status, and the availability of water sources will be presented to indicate the effects of randomization and comparability of the intervention groups.

Comparison of rates: Cluster level incidence rates are used as the unit of analysis to compare incidence rates between intervention and control groups. Given the cluster size exceeding  $N=10$  Pearson  $\chi^2$  test can be used to compare cluster or group level incidence rates (Donner and Klar 1994). The calculations of Pearson  $\chi^2$  accounts for the degree of intracluster correlation and the variance inflation due to clustering (Klar et al. 1995).

Bias and Confounding: Randomization procedures throughout the hierarchical structure of this cluster-randomized trial should make intervention groups comparable at baseline at cluster- and village level. Any bias resulting from incomplete randomization or from monitoring specific village factors that relate to compliance as well as unpredictable outside factors (e.g. media) will be dealt with in the analysis.

Evaluation of effect modification will be achieved by including multiplicative interaction terms in a generalization of Poisson regression analysis adapted for the residual correlation of the total number of diarrheal episodes among children in the same cluster (see details below). The effects of well known factors that act as effect modifier such as the presence /absence of sanitary facilities in the compound, or previous exposure to health education will be considered. Preliminary assessment of interaction will be done by stratification and decision will subsequently be made whether to include interaction terms as indicators in the Poisson regression analysis.

Multivariate statistics: Simple comparisons of rates will be done using software that is designed to accommodate the complexity of a cluster randomization design (SUDAAN). Simple Poisson regression cannot be used to make inferences about the effect of treatment in cluster randomization trials since it is constructed on the assumption that the conditional responses of individuals are statistically independent. An extension of the Poisson regression, generalized estimation equation approach (GEE) will be employed (Liang and Zeger 1986). For these regressions, the number of episodes of diarrhea for each child will be the outcome and, although we will report the inference based on robust estimates of the variance, we will assume the correlation within a cluster to be compound symmetry in the estimation procedure. We can possibly reduce the variance of the estimate of the treatment effect by adjusting for both baseline risk factors measured at either cluster level (cluster size, SES) or individual level (e.g. age, sex) (Klar et al. 1995). This becomes particularly important if the distribution of these covariates, by bad luck, are not similarly distributed in the treatment and the control arms of the study. We will also explore the strength of possible effect modification by looking at the inference of multiplicative interaction terms discussed above. We will account for the fact that some children will have different total time at risk due to our definition of an episode discussed in Section D.3 by including an offset term in the regression models that is the natural log of the total time (in days) that a child was at risk of diarrhea. Finally, the regression model will return parameters that can be interpreted as the marginal ratio of diarrhea rates relative to the variable of interest. Specifically, the models will return an estimate of the ratio of diarrhea rates in populations that have the treatment versus those with the controls, all other factors (covariates) being equal in the two populations. If we find significant effect modification with treatment, then the model will return rate ratios specific to levels of the interacting variable(s), e.g., the ratio of rates in treatment versus control among populations with unsanitary facilities.

A secondary analysis will consider estimation of the attributable fraction of diarrhea due to specific pathogens. In this case, the outcome data is the presence or absence of diarrhea among the stool samples and the explanatory variables of interest are the presence/absence of particular pathogens. In this case, we have two levels of replication: 1) the possibility of more than one stool sample (diarrhea) per child and 2) 10 children (with specimen tested) within the

cluster (village). Given the very real possibility residual correlation among the replicates, we again will use a GEE regression approach. In this case, our outcome is binary (presence/absence of diarrheal stool sample) so we will use the GEE generalization of logistic regression. We will choose the variables to adjust for (and those to consider as effect modifiers) similar to that described above (note, that treatment now plays the roll of a potential effect modifier).

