Study design and the potential for confounding : For the control of confounding, we apply randomization at all levels (for the selection of villages and participants and for the allocation of the intervention). Additionally, we have matched villages on the pre-intervention outcome (diarrhea rate) as suggested by one of the reviewers. These two strategies (randomization and matching) are the most effective ways to reduce the variance of our effect estimate and to remove the potential bias due to confounding. In studying the effect of our intervention, confounding could result, as noted by the reviewer, if we differentially assigned treatment to those villages with either higher or lower inherent rates of diarrhea. However, by matching the villages on the baseline incidence of diarrhea the potential for confounding by differential initial conditions is greatly reduced. In further response to the reviewer, we now will further reduce the potential for mismatching villages by matching them on the basis of an estimate of diarrhea rates for eight weeks (previously based on a single 7 day recall diary) (Section D.6.b.). We will apply our newly adapted and pretested daily morbidity diaries combined with weekly home visits. This will reduce any misclassification bias in the pairing of villages prior to random assignment of the intervention. Based on our own experience in Bangladesh and Bolivia (Appendix F and F2) and that of others (Samanta and Van Wijk 1998), we will assess village characteristics that could be related to compliance by recording factors such as existing collective community efforts (e.g. commitments to community development, income generating projects, community banking accounts, cultural factors), to adjust for them in the analysis stage.

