#### **D.6.b. Baseline morbidity surveys in the trial villages to estimate the period prevalence of diarrheal episodes in children <5 years and to facilitate randomization of communities**

At the beginning of the study, a prospective eight week survey among households with children <5 years will be conducted in the 22 villages to estimate the proportion (period prevalence) of child diarrheal illness. The usually short duration of a diarrheal episode and the short incubation period for a new episode will allow us to estimate the incidence density of child diarrhea in each cluster (i.e. village-cluster incidence rate) at baseline. The main purpose of obtaining a prevalence estimate is to facilitate matching of study sites according to the occurrence of reported diarrhea in children. This change (previously a 7 day cross-sectional survey but now an eight week longitudinal measurement) was done in order to address a comment in the prior review about improving our strategy to minimize possible differences in confounding factors between villages at baseline. Sites ranked by eight week baseline diarrhea rates are then grouped in pairs and the introduction of the SODIS intervention is randomly allocated to one of them. Thus, 11 sites receive the intervention, 11 other sites serve as controls. This high level randomization of the village-clusters to the SODIS intervention is the single most effective strategy to limit bias in the estimation of the intervention effect (Murray 1998) (cf. also Section D.7.). PCI will adapt to the random allocation of the SODIS intervention and will start activities in the villages of the intervention arm after our baseline survey has been completed.

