| 50%                                     | (2.5 episodes)  | 3.4                                       | 4.5      | 6.5      |

**Design effect:** Ignoring clustering in this trial would turn the trial design into that of a classical clinical trial with individual randomization. The required sample size in terms of person-years of observation (y) is calculated as,

$$y = (z_{a/2} + z_B)^2 \times (R_0 + R_1) / (R_0 - R_1)^2, \text{ and}$$

would result in 23.6 year of person-time of observation in each cluster and in a design effect of ~2.4. (23.6/10)

From those calculations we conclude the following:

**Number of clusters and subjects per cluster:** We assume that the incidence rate of diarrhea in the control villages remains constant at 5 episodes/child/year and that we require 80% power ( $z_a = 0.84$ ) of detecting a significant difference ( $p < 0.05$ ;  $z_{a/2} = 1.96$ ) if the intervention reduces diarrheal incidence by 33%. We will achieve a minimum of 10 person-years of observation in each cluster, which amounts to 10 subjects per cluster observed for the duration of 12 months. Finally, considering a conservative between-cluster variation ( $k=0.2$ ) we would need 9 villages each in the intervention and control group. Based on previous experience in our Bangladesh trial (Hobbins et al. 2000a) we consider a drop out rate of one to two villages per study group and thus adjust final sample size to 22 villages (clusters); 11 in each treatment arm.

Finally, we have included 30 children in each village with the following justification:

i.) few marginal costs arise in investigating more children in each village;

- ii.) this allows us to compensate for loss of follow up of individuals;
- iii.) the study is powered to maintain its ability to detect even a 16% reduction of diarrheal incidence from 5 to 4.2 episodes at a between cluster variation of  $k=0.12$  (cf. Table 2. detailed Calculations not shown).

Thus, overall 660 households, 30 in each of the 22 villages and each with an index child under the age of 5 years enrolled in the trial will be participating in the study.

The following additional information on different parameters was considered in the sample size calculations above:

1. About 15% of the rural population in the study area are children under 5 years.(Centro Desarrollo Agropec., 1994).

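### Villages are pair-matched on baseline diarrhea rate, but D.9 uses neither the pairs nor that rate, so its standard errors are too large to the extent that matching works

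*Protocol*

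**What the plan says.** **Design.** Protocol D.1 and D.6.b restrict the randomisation. "Sites ranked by eight week baseline diarrhea rates are then grouped in pairs", and one village of each pair is drawn for SODIS. The introduction to the revised application gives variance as one reason: "These two strategies (randomization and matching) are the most effective ways to reduce the variance of our effect estimate". It and D.10 also present matching as protection against baseline imbalance and confounding.

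**Analysis.** D.9 names two comparisons of the arms.
- At village level, "Cluster level incidence rates are used as the unit of analysis to compare incidence rates between intervention and control groups", using a Pearson chi-square corrected for intracluster correlation.
- At child level, a Poisson GEE with compound symmetry within village, robust variance and a log time-at-risk offset. Variance may be reduced further by "adjusting for both baseline risk factors measured at either cluster level (cluster size, SES) or individual level (e.g. age, sex").

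No pair term, paired test or baseline village diarrhea rate appears. Section A mentions mixed effects models and D.5 mentions adjustment for cluster sampling; both concern clustering within villages, not pairing of villages.

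**The concern.** Ranking and pairing on a prognostic rate makes the two arms' mean rates move together. The true variance of the treatment contrast is then smaller than that of two independent groups of 11 villages. An analysis that treats the villages as two independent groups still charges the full between-village variance to the contrast.

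D.9 fixes the test, working correlation, variance estimator, offset and example covariates, so this is a stated choice that does not follow the stated randomisation. The usual triggers for adjustment would not pick up the missing variable either. D.9 stresses adjustment when covariates are unequal by chance, and D.10 speaks of confounders that happen to differ. The matching variable is balanced by construction.

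At stake is a moderate SODIS effect being reported as not significant although the design could have shown it.

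**Working it through.** **1. The plan's own figure.** Inputs from D.8: "we require 80% power ( $z_a = 0.84$ ) of detecting a significant difference", two-sided 5% (z = 1.96); "incidence rate of diarrhea in the control villages remains constant at 5 episodes/child/year"; an effect "if the intervention reduces diarrheal incidence by 33" per cent, so R1 = 3.333; and "We will achieve a minimum of 10 person-years of observation in each cluster". With k = 0.2:

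c = 2 + (1.96 + 0.84)² × {(R0 + R1)/y + k²(R0² + R1²)} / (R0 − R1)²
= 2 + 7.84 × {8.333/10 + 0.04 × 36.11} / 2.778 = 8.43, rounded up to 9 per arm.

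This reproduces D.8. There k is the between-village coefficient of variation within an arm, so the calculation takes no credit for matching. At D.8's upper value k = 0.3, with the planned 30 person-years per village, the formula gives 2 + 7.84 × (0.278 + 3.25)/2.778 = 11.96, against 11 enrolled.

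**2. Standard error with and without the pairs.** For 11 villages per arm, 30 person-years each and k = 0.3:
- Unpaired: √{(8.333/30 + 0.09 × 36.11)/11} = √(3.528/11) = 0.566.
- Paired: subtract 2ρ·s0·s1, where s0² = 5/30 + 0.09 × 25 = 2.417, s1² = 3.333/30 + 0.09 × 11.11 = 1.111, and s0·s1 = 1.639. At ρ = 0.5: √{(3.528 − 1.639)/11} = 0.414.

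Here ρ is the correlation of follow-up rates within a pair. The documents do not give it, so a range is shown.

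| ρ | Paired SE | Unpaired SE ÷ paired SE |
|---|---|---|
| 0 | 0.566 | 1.00 |
| 0.2 | 0.511 | 1.11 |
| 0.3 | 0.481 | 1.18 |
| 0.5 | 0.414 | 1.37 |
| 0.7 | 0.335 | 1.69 |

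A paired t-test has 10 df instead of 20. Its interval is narrower only above ρ of about 0.12. At ρ = 0 and k = 0.3, power for a 33% reduction is 76% paired against 80% unpaired.

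**3. Simulation of the whole design.** Villages have log-normal rates and 30 children each, with control rate 5 per child-year. Eight-week Poisson counts are ranked and paired, arms are drawn within pairs, and follow-up is 52 weeks. Assumptions not in the documents: a child-level coefficient of variation of 0.7, and the correlation r between a village's true baseline and follow-up rates. Results at k = 0.3:

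| r | Unpaired SE against true SD | Type I error, robust GEE |
|---|---|---|
| 0 | correct to within about 3% | 7-8% |
| 0.5 | about 12% too wide | 5-6% |
| 0.8 | about 30% too wide (0.142 against 0.107-0.108) | about 2% |

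At r = 0.8 the unpaired village-level test has a type I error of about 1%.

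Steps 2 and 3 agree. On the log scale the ratio is about 1/√(1 − ρ), so 12% corresponds to ρ = 1 − 1/1.12² = 0.20 and 30% to ρ = 1 − 1/1.30² = 0.41. A baseline correlation of 0.5 therefore yields a much weaker within-pair correlation.

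**4. Power.**

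| Setting | As planned | Using the matching |
|---|---|---|
| 33% reduction, k = 0.3, r = 0.8 | 83-88% | 92-94% |
| 25% reduction, k = 0.3, r = 0.8 | 49-59% | 67% paired, 73% baseline-adjusted |
| 25% reduction, k = 0.3, r = 0.5 | 57% (GEE) | 55% paired, 58% baseline-adjusted |
| 33% reduction, k = 0.2 | about 95% or more at every r tried | similar or higher |

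Ranges as planned cover the unpaired t-test and the robust GEE. The 25% effect is illustrative; the protocol does not set it.

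**The case against.** A reader might infer that the standard errors will simply be too large, that the 5% test will run far below 5%, and that the precision bought by matching is lost. The documents do not support this.

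- **The condition is unknown.** All of it needs an eight-week rate from one part of the year to predict the annual rate well. No such correlation is given, and D.10 itself expects seasonal infection patterns.
- **The GEE is not always conservative.** With 22 villages and an uncorrected robust variance, its type I error is near nominal at r = 0.5 and 7-8% at r = 0.
- **The estimate keeps the benefit.** Balance and the smaller true variance remain; only the reported uncertainty fails to show them. Protection against confounding, the other stated purpose of matching, is untouched.
- **Planned power does not rest on the matching**, as step 1 shows, and is ample at the design point.
- **The text leaves some room.** The covariates in D.9 can be read as examples, and village rates as the unit of analysis would be compatible with a paired test.

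The first four points stand and limit the finding to a conditional one. The last stands only in part: a plan that names its adjustment variables and omits the one on which villages were matched has not provided for it.

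**Conclusion.** The point holds in conditional form. D.9 does not carry the restricted randomisation into either analysis. To the extent that matching works, the standard error, confidence interval and p-value are too conservative, while the point estimate keeps the gain.

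The overstatement at k = 0.3 runs from essentially none at r = 0 to about 30% at r = 0.8, and rests on the assumed child-level variation of 0.7. The power loss matters if k is near D.8's upper value or the effect is smaller than 33%, not at the design point. If matching is weak, the error reverses for the uncorrected GEE, which becomes slightly anti-conservative. The omission introduces no bias in the estimate. It should be fixed because the remedy is cheap, but it does not threaten the trial's validity.

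**What to change.** In D.9, prespecify the log eight-week baseline village rate as a covariate in the primary analysis. One form is log village incidence regressed on arm and log baseline rate, with a t reference on 22 − 3 = 19 df. Put the same covariate in the child-level GEE, with a small-sample correction for 22 clusters. Support both with a permutation test that swaps arms within pairs.

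Do not rely on a paired t-test alone: its 10 df lose power when matching is weak, and D.8 expects one or two villages per arm to drop out, which would break pairs. The covariate keeps a village whose mate is lost.

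The cost is wording and one degree of freedom, since the rate is already collected. At r = 0, adjustment costs under one percentage point of power in the settings tried. The change should be made before outcome data are analysed.

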Sample size: Given the relatively large size of the study with 22 clusters and given that randomization will be employed at all levels we hope that residual bias will be measurable. While randomization of even small numbers of villages to intervention and non-intervention group ensures equal probability of assignment for each group, it cannot ensure that all potential sources of bias will be equally distributed. Pending our baseline field work in the trial villages, we have to anticipate a heterogeneity of the occurrence of baseline diarrheal diseases (our outcome) among the different village-clusters. A simple random assignment to the intervention or control group is unreliable to achieve baseline comparability among the study conditions. This applies particularly if the number of clusters in each condition is relatively small, as is in our study (N=11 villages). We thus, employ an *a priori* matching of the villages according to the baseline incidence of childhood diarrheal illness before random assignment of the intervention to one of the pairs.

Diarrheal episodes as outcome measure: Our outcome measure (diarrheal episodes) is subject to the influence of numerous measurable and unknown factors particularly in developing countries. By incorporating the suggestion made in the earlier review for *a priori* matching on the endpoint (baseline incidence of diarrhea) we have attempted to control for the effects of a number of unknown confounding factors as well as some of the factors that are difficult to assess such transient risk factors. We will be able to adjust for any relevant confounding factors that might randomly differ significantly in the groups.

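### GEE rate ratio rests on a robust variance with 22 villages and no stated small-sample correction, so its nominal 5% level is not assured

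*Protocol*

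**What the plan says.** D.9 (Multivariate statistics) sets out a Poisson GEE, citing the original GEE paper. The outcome is each child's episode count, the working correlation within village is compound symmetry, and the offset is log time at risk. On variance it says "although we will report the inference based on robust estimates of the variance". It adds that precision may possibly be gained by "adjusting for both baseline risk factors measured at either cluster level (cluster size, SES) or individual level (e.g. age, sex"), and that this matters more if covariates turn out unbalanced. It names no finite-sample correction, degrees of freedom or reference distribution for this test, and sets no limit on the number of village-level terms.

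On the number of clusters, D.8 says to "adjust final sample size to 22 villages (clusters); 11 in each treatment arm", after allowing for the loss of one to two villages per arm. D.10, explaining why simple random assignment is unreliable, says "This applies particularly if the number of clusters in each condition is relatively small, as is in our study (N=11 villages"). D.6.b pairs the villages on their ranked eight-week baseline diarrhea rate. Neither the pairs nor that baseline rate is named in the D.9 model.

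Two other analyses are named. D.9 (Comparison of rates) uses village incidence rates as the unit of analysis with a clustering-adjusted chi-square. Section A (Specific Aims) speaks of mixed-effects models.

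**The concern.** The sandwich variance is estimated from as many independent contributions as there are villages. With 22 of them it is biased downward, because fitted residuals are smaller than true ones, and every village-level parameter removes more residual variation. Read against z = 1.96, the interval is too narrow and the p-value too small.

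The pair-matching acts in the opposite direction. If the baseline rate predicts follow-up and the model omits it, the true variance of the treatment contrast is smaller than the model's variance implies, and the test becomes conservative. The two errors need not cancel, and how far they do is unknown before the data are seen.

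At stake is whether an ineffective programme is declared effective more often than 5% of the time, or an effective one is missed through an overstated variance. The protocol expects its result to influence international support for the method.

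**Working it through.** **Inputs from the protocol.** 22 villages, 11 per arm (D.8); 30 children per village (D.8); control rate 5 episodes/child/year (D.8); two-sided 5% with z = 1.96 (D.8); k = 0.2 in the village count and 0.3 or lower as the ceiling (D.8); one to two villages lost per arm (D.8).

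**Assumptions not in the protocol.** A z reference for the GEE test; child-level CV 0.6 to 0.9; zero to four village covariates; and the correlation between baseline and follow-up village rates, which was varied.

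**Step 1: the plan's own figure.** With y = 10, k = 0.2, R0 = 5 and R1 = 3.333:

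c = 2 + (1.96 + 0.84)² × {8.333/10 + 0.04 × 36.11} / 1.667² = 2 + 7.84 × 2.278 / 2.778 = 8.43

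This rounds up to the stated 9 per arm. The plan's figure is reproduced and is not in dispute.

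**Step 2: expected size of the bias by hand.** Let J be the number of villages, q the number of village covariates and P = 2 + q the number of village-level parameters. With equal leverage, the uncorrected sandwich variance averages about (J − P)/J of its target. Comparing with 1.96 is then like comparing a t statistic on J − P degrees of freedom with 1.96 × √((J − P)/J).

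| J | q | Effective cut-off | Rejection under the null |
|---|---|---|---|
| 22 | 0 | 1.96 × √(20/22) = 1.869 on 20 df | 7.6% |
| 22 | 1 | 1.96 × √(19/22) = 1.821 on 19 df | 8.4% |
| 22 | 2 | 1.96 × √(18/22) = 1.773 on 18 df | 9.3% |
| 22 | 4 | 1.96 × √(16/22) = 1.671 on 16 df | 11.4% |
| 18 | 0 | 1.96 × √(16/18) = 1.848 on 16 df | 8.3% |
| 18 | 4 | 1.96 × √(12/18) = 1.600 on 12 df | 13.6% |

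This ignores unequal leverage, so it is a rough guide.

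**Step 3: simulated null trials, matching uninformative.** Log-normal village rates, gamma child heterogeneity (CV 0.6), Poisson counts, uncorrected robust variance, z = 1.96. Entries are percentages rejected.

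| Setting | q = 0 | q = 1 | q = 2 | q = 4 |
|---|---|---|---|---|
| 22 villages, k = 0.2 | 7.7 | 8.4 | 10.0 | 11.2 |
| 22 villages, k = 0.25 | about 7 | 8-9 | 10-12 | 13-14 |
| 22 villages, k = 0.34 | 8.6 | 9.1 | 10.8 | 13.8 |
| 18 villages, k = 0.25 | 8.9 | 10.1 | 11.1 | 14.7 |
| 22 villages, k = 0.25, GEE on individual data with age and sex | 7.1 | 8.4 | 10.0 | 11.6 |

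Monte Carlo error at 10% is about ±1.4 points with 1,800 runs and ±2.1 with 800 (the individual-data row). Replacing z by t on 21 df without correcting the variance still gives about 7-12% for one to four covariates.

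**Step 4: matching informative, k = 0.25.** Here q counts covariates other than the baseline rate.

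| Correlation of baseline and follow-up | Baseline rate in model? | q = 0 | q = 1 | q = 2 | q = 4 |
|---|---|---|---|---|---|
| 0.5 | no | about 5 | 6-7 | 7-9 | 11-12 |
| 0.7 | no | about 3 | 4-5 | 5-6 | 7-11 |
| 0.5 | yes | 8.7 | 9.8 | 11.7 | 13.6 |
| 0.7 | yes | 8.6 | 11.9 | 11.8 | 14.6 |

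Simulation with child CV 0.9 gives the same pattern: 8.5-9.6% with the baseline rate alone, 11-12% with two more covariates and 13-15% with four more. With no baseline covariate it gives 0.5-7%, depending on how well baseline predicts follow-up.

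**Step 5: after correction.** A Kauermann-Carroll-type or degrees-of-freedom-corrected variance with t on villages minus parameters gives about 4.5-7% in the settings of Step 3, and about 5-7% in Step 4 with the baseline rate in the model. If the baseline rate is left out and the correlation is 0.7, the corrected test rejects only about 2-4%. Correcting the variance alone is therefore not enough. A paired t-test on the 11 within-pair log-rate differences gives 5.5%. Entering pair indicators while keeping the uncorrected variance gives about 22%.

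**The case against.** The strongest reply is that the protocol never says the variance is uncorrected. It is silent, and a correction could sit in a statistical analysis plan that is not shown. That stands in part: uncorrected is an inference from the wording and the method cited. But the protocol does not leave the variance open. It names the robust estimator and cites a paper whose default carries no such correction.

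A reader might infer that the trial's main test has a false-positive rate of 9-14%. The documents do not support that, for four reasons:

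- Adjustment is only a possibility in D.9, and without it the rate is about 7-8% or lower.
- The baseline village rate is not a listed covariate. The results that hold whatever the strength of matching are those that include it.
- Informative matching left out of the model lowers the rate, possibly below 5%.
- D.9 also offers a village-level chi-square and Section A names mixed models, so the GEE is not clearly the one main analysis. The 5% in D.8 belongs to a calculation on village summaries, not to this test.

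Nor does it follow that error is at least doubled. One covariate gives 8-9% with 22 villages, and reaching 10% generally takes two or more. All these objections stand as limits on size and scope. None supplies the missing correction.

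**Conclusion.** The point holds in a conditional form. As written, the GEE rate ratio has no assured 5% level. With a z reference, k about 0.2-0.3 and child-level CV 0.6-0.9, the null is rejected about 7-8% of the time unadjusted and about 8-14% with one to four village covariates when matching is uninformative. The range is about 8-15% when the baseline rate is in the model. With informative matching left out, the unadjusted rate can drop to about 3% or less. The direction of the sandwich bias is certain. The net size depends on choices the protocol leaves open and on how stable village rates are. This should be corrected before analysis, but it does not show that the trial's principal conclusion is invalid.

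**What to change.** In D.9, report the GEE with the baseline village diarrhea rate (the matching variable) as a covariate, a small-sample-corrected robust variance (for example Kauermann-Carroll or Fay-Graubard), and a t reference with villages minus village-level parameters as degrees of freedom. Limit further village-level covariates to one or two. Alternatively, take the p-value from a permutation test that re-allocates treatment within the 11 pairs.

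The cost is wording plus wider intervals. Approximating the correction by (t/1.96) × √(J/(J − P)) with 22 villages, the widening relative to an uncorrected fit of the same model is:

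- treatment only: (2.086/1.96) × √(22/20) = 1.12;
- with the baseline rate: (2.093/1.96) × √(22/19) = 1.15;
- with one further covariate: (2.101/1.96) × √(22/18) = 1.19;
- with two further covariates: (2.110/1.96) × √(22/17) = 1.22.

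That is roughly 10-20%, slightly more at the upper limit of covariates. If the baseline rate is predictive, including it should recover some of that width.
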